#### Patient recruitment and power calculation

We plan on recruiting about 250 patients a year in each participating CSSS, for a total of 3500 patients over 28 months. Assuming that recruitment rate is constant, we estimate that the 2000 patients recruited in the first 16 months could be the object, during the study, of at least three observations for data collected using questionnaires, and at least six observations for clinical data (Table 1). For the 1500 patients recruited during the last 12 months of recruitment, we will have two observations for data collected using questionnaires and at least four observations for clinical data. We expect that an initial sample of 3500 subjects, with an attrition rate of 20%, would ensure 2800 subjects available for analyses over two time measures. This sample size would allow detection of a difference in average between two territories that is about 0.14 in standard deviation units in longitudinal linear models, and about 7%, with a power of 80% at the 0.05 significance level in logistic models [42,43]. These calculations are conservatively based on the number of subjects measured twice; use of effective covariables or of a higher number of observations per subject should lead to an increase in the power of models.

**Table 1 T1:** Patient recruitment and numbers of data collected

Number of patients	Questionnaires (services utilization, affiliation to primary care physician, chronic illness monitoring, self-management, quality of life)	**Registry ****data ****(biological measures and lifestyle habits)**
500 patients recruited in first 4 months	0, 12, 24 and 36 months	0, 3, 6, 12, 18 and 24 months

500 patients recruited in months 5 to 8	0, 12 and 24 months	0, 3, 6, 12, 18 and 24 months

500 patients recruited in months 9 to 12	0, 12 and 24 months	0, 3, 6, 12, 18 and 24 months

500 patients recruited in months 13 to 16	0, 12 and 24 months	0, 3, 6, 12, 18 and 24 months

500 patients recruited in months 17 to 20	0 and 12 months	0, 3, 6, 12 and 18 months

500 patients recruited in months 21 to 24	0 and 12 months	0, 3, 6 and 12 months

500 patients recruited in months 25 to 28	0 and 12 months	0, 3, 6 and 12 months

**Indicators concerning the impact on medical practice **will be measured for participating general practitioners using a 15-minute self-administered mail-in questionnaire, in French or in English, the first time one of his or her patients attends the cardiometabolic risk education centre, and then at 12, 24 and 36 months (Additional file 5 and Additional file 6). In addition to questions pertaining to physicians' sociodemographic and professional characteristics, the questionnaire also documents the organizational characteristics of their clinics using questions from the 2010 survey of primary care clinics used in our previous project [36]. One section of the questionnaire deals with physicians' practices regarding management of patients with diabetes or hypertension; these questions are adapted from the questionnaire by Nutting et al. [44]. The questionnaire for physicians administered at 12, 24 and 36 months includes several questions on their assessment of the PCMR: participation in the program, impacts on their patients and on their practice, relationships with specialized services, strengths and weaknesses of the program, as well as barriers and facilitating factors. The data analysis strategy will be similar to the one used to assess the effects of the program on patients. Physician and clinic characteristics will be utilized as covariables to construct regression models that measure the program's effects on their management of chronic diseases and their perceptions of the effects on patients and on their own practice.

#### Objective 2

Two elements are required to meet the goals. The first consists in assessing the level of PCMR implementation in various CSSS based on four criteria: 1) completeness of the components with regard to the program initially planned by the ASSSM; to assess the degree of implementation, we will measure the differences between the program planned by the ASSSM and the one actually implemented in CSSS; 2) intensity of the effort made to conduct program activities (e.g. number of training sessions, number of patients); 3) integration of the PCMR into CSSS program activities; and 4) program penetration rate among the targeted populations. This will be estimated by calculating the proportion of patients with diabetes or hypertension followed in the PCMR among patients with diabetes or hypertension in each participating CSSS territory (estimated using the medical services and hospitalizations administrative data).

The second element includes an analysis of factors influencing program implementation [45]. The goal of the analysis is to understand how and why the PCMR has evolved and adapted to its context over time. It will put into perspective what program elements that are truly implemented contribute to the effects produced and will evaluate the generalizability potential of the program to other contexts. In terms of contextual determinants of program implementation, we looked to the conceptual framework on factors to consider to produce change in organizations, developed by Champagne [46]. We consider that implementation results from the climate in which the program is implemented (itself influenced by management strategies and incentives used), the level of trust and involvement of stakeholders, the organizational structure that is likely to help or hinder implementation, and collective leadership and training. This component will also examine contextual factors that explain PCMR implementation in terms of the influences of various actors from the local services network. The ASSSM and the CSSS can have a coercive influence because of their position of authority and the significant resources they contribute. Through their professional associations, professionals collectively and individually have normative influences. In each local services network, there are also dominant organizations whose practices are considered to be exemplary by other partners, who tend to emulate them. These dominant organizations have a mimetic influence (e.g. FMG, network clinics).

Data will be collected in three phases, as per the program implementation stages. Semi-structured interviews with individuals from the ASSS and CSSS responsible for program implementation are scheduled for the beginning of the project (start-up phase). They will provide an initial portrait of regional services organization related to the activities of the program being implemented and will document the program components (objectives and purposes, roles and actors involved, resources and activities). They will also be used to define the dynamics in each implementation site. Interviews with respondents from each territory will focus on local historical contexts of interventions with people at risk of or who have diabetes or hypertension; organizational contexts of the CSSS; PCMR activities already in place and their components; local resources allocated; number of medical clinics and physicians involved; and number of patients targeted by the program. A second and third round of semi-structured interviews with local and regional respondents will be conducted 20 and 40 months after the beginning of the program. They will document PCMR activities actually implemented and degree of program implementation, activities set up to integrate the PCMR into the CSSS's regular activities, and obstacles and facilitators encountered. The questionnaires for physicians will also document barriers and facilitators. These contextual determinants will be grouped by dimension and conveyed with descriptive variables. The interview grids used at the beginning of the implementation of the project are included in Additional files 7a and 7b. Data collection tools that will be used 20 and 40 months after the beginning of the program will be constructed after analysis of the data collected at the beginning of the implementation of the project.

Based on the information collected throughout the project, a descriptive analysis of each case (implementation setting) will be performed. Six monographs, one for each setting, will describe the phases of PCMR implementation and its explanatory factors.

#### Objective 3

Two approaches will be used to attain this objective. The first is designed to complement the analysis proposed in Objective 2. Using the material compiled in the monographs, quantitative variables and categorical taxonomic variables will be created and integrated into regression analyses explaining the effects of the program. Regression models will be built to assess the influence of the variables pertaining to PCMR set up and implementation in the various CSSS on the effects observed among patients, controlling for degree of exposure to PCMR, patient characteristics and the characteristics of primary care clinics where they are seen. Given the low number of upper level units (6 CSSS), variables linked to CSSS will be considered as fixed effects in regression models. Linear regressions will be constructed for continuous dependent variables, while logistic models will be used for dichotomous dependent variables and multilevel longitudinal models for dependent variables that are the object of repeated measures. A similar analysis strategy will be used to assess the influence on medical practice of variables that reflect PCMR set up and implementation in various CSSS.

The second approach will be interpretive: from the material used to produce the monographs, participants' statements on the relationship between program effects and components will be noted and analyzed. Conclusions drawn from these two approaches will be validated in discussion groups.

#### Objective 4

This objective concerns the PCMR's influence on interorganizational collaboration and networking among local services networks. We are interested in mechanisms for collaboration that exist between CSSS and primary care organizations in the territories and health care and services providers, as well as their evolution over time. We will use the framework developed for our previous project [36]. Interorganizational collaboration within local services networks will be documented at the beginning of the project, based on the results of our previous project [36], which looked at this issue for CSSS territories in Montréal in 2010 (questionnaire in Additional file 8). A questionnaire administered to key CSSS informants 40 months after project onset will document the evolution of interorganizational collaboration within local services networks in relation to PCMR implementation (Additional file 9). By becoming a model of service integration, the PCMR is in fact likely to form a best practice that has a mimetic influence on local services network partners, and eventually lead to the creation of other networks (e.g. for COPD) and, more generally, to interorganizational collaboration. The questionnaire will be adapted from questionnaires used in our previous project [36] to explore territorial contexts. Questions on the PCMR's influence on interorganizational collaboration and networking within local services networks will also be included in the final questionnaire for physicians participating in the program.

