
Use of health services by patients in the PCMR will also be documented with medical administrative data (medical services, hospitalizations, emergency room visits), using the patient's health insurance number to match medical administrative data to data from the regional computerized registry on chronic illnesses and to his or her survey data.

Regression models will be built to assess the program's effects on patients, in terms of biological parameters, lifestyle habits, health services utilization, chronic illness follow-up, self-management, quality of life and care experience, based on the CSSS, degree of exposure to the program, patient characteristics, and organizational characteristics of primary care clinics where patients are seen. Particular attention will be paid to patients' sociodemographic characteristics (male/female, age, income, education) in terms of equity of access to services. Linear models will be constructed for continuous dependent variables (e.g. before-after intervention differences in HbA1c or BP). Logistic models will be used for dichotomous dependent variables (e.g. clinical targets achieved or not by the end of the intervention, dichotomized indices). Longitudinal analyses will enable us to model the evolution of dependent variables throughout the follow-up period. These analyses will be performed using multilevel models (Generalized Linear Mixed Models) [41] in which individual repeated observations will be nested within patients. We will thus be able to control for certain fixed subject characteristics as well as for time-varying covariates.

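### The detectable differences given for two territories (0.14 SD and 7%) do not follow from the stated sample size; a simple pairwise contrast detects about 0.18 SD and up to about 9 points

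*Protocol article*

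**What the plan says.** All the planning figures are in the Protocol article, Patient recruitment and power calculation.

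- Recruitment: "We plan on recruiting about 250 patients a year in each participating CSSS, for a total of 3500 patients over 28 months".
- Analysable sample: 3500 subjects, "with an attrition rate of 20%, would ensure 2800 subjects available for analyses over two time measures".
- Continuous outcomes, for longitudinal linear models: "This sample size would allow detection of a difference in average between two territories that is about 0.14 in standard deviation units".
- Binary outcomes: "and about 7%, with a power of 80% at the 0.05 significance level in logistic models".

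Under Indicators, data sources and analyses, the continuous example is a before-after difference in HbA1c or blood pressure. For binary outcomes: "Logistic models will be used for dichotomous dependent variables (e.g. clinical targets achieved or not by the end of the intervention". Under Objective 3 the territories enter the models as fixed effects: "Given the low number of upper level units (6 CSSS), variables linked to CSSS will be considered as fixed effects in regression models".

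The power paragraph does not give the number of patients per territory, the within-patient correlation, the reference proportion or the sidedness of the test.

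**The concern.** The figures are labelled as differences between two territories, yet the only sample size beside them is the total over six. Two of six equal territories hold one third of the patients, and the usual formula for that contrast gives larger detectable differences than those printed.

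This matters because the Design section makes variation of effects among the six settings part of the purpose of the quantitative strategy, and Objective 3 then tries to explain that variation. If the true sensitivity for a pair of territories is nearer 0.18 SD or 9 points, a non-significant pairwise difference of 0.14 SD or 7 points could be taken as well-powered evidence of no difference when its power is little better than one half.

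**Working it through.** **Inputs.** From the power paragraph: 250 patients per year per territory, 28 months, 20% attrition, 80% power, 0.05 significance. Six territories. Two-sided testing is assumed, since sidedness is not stated.

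**Sample size.** 6 × 250 × 28/12 = 3500, so the plan implies equal territories. 3500 × 0.8 = 2800, and 2800/6 = 466.7 per territory.

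**Trying to reproduce 0.14 SD for two territories, one value per patient.** Detectable difference = (1.960 + 0.842) × √(1/n₁ + 1/n₂).
- 467 vs 467: 2.802 × √(2/466.7) = 0.183 SD. One-sided: 0.163.
- Before attrition (583 vs 583): 0.164 two-sided, 0.146 one-sided.

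None of these gives 0.14. Power for 0.14 SD with 467 vs 467 is Φ(0.14/√(2/467) − 1.960) = Φ(0.18), about 57%. Reaching 80% would take 2 × (2.802/0.14)² ≈ 801 patients per territory.

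**Two measures per patient, 467 vs 467.** If the SD is that of the change itself, the figure stays at 0.183 whatever the correlation ρ. In SDs of a single measurement, 0.183 is multiplied by √(2(1−ρ)) for a change score, √(1−ρ²) for a baseline-adjusted comparison, or √((1+ρ)/2) for the average of the two measures.

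| Analysis | ρ = 0.3 | ρ = 0.5 | ρ = 0.7 | ρ that gives 0.14 |
|---|---|---|---|---|
| Change score | 0.217 | 0.183 | 0.142 | 0.71 |
| Baseline-adjusted | 0.175 | 0.159 | 0.131 | 0.65 |
| Average of both measures | 0.148 | 0.159 | 0.169 | 0.17 |

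**Trying to reproduce 7% for two territories, end-of-intervention attainment, unadjusted.** The difference d = p₂ − p₁ solves d = 1.960√(2p̄(1−p̄)/n) + 0.842√([p₁(1−p₁) + p₂(1−p₂)]/n), with n = 467 and p̄ the mean of p₁ and p₂.

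| Lower proportion | 10% | 14% | 20% | 30% | 50% | 70% | 79% |
|---|---|---|---|---|---|---|---|
| Detectable difference (points) | 6.2 | 7.0 | 7.8 | 8.7 | 9.1 | 8.0 | 7.0 |

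Seven points is therefore detectable only if the lower proportion is at or below about 14%, or at or above about 79%. Near 50%, power for 7 points is about 57%.

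**Settings that give both printed figures together.**
- One territory against the other five pooled (467 vs 2333): 2.802 × √(1/466.7 + 1/2333.3) = 0.142 SD; × 0.5 = 7.1 points near 50%. This is not a contrast between two territories.
- Two territories compared on the average of entry and follow-up values: at ρ = 0.17, 0.140 SD and 2.802 × √((0.5/466.7) × 1.17/2) = 7.0 points near 50%; at ρ = 0.2, 0.142 SD and 7.1 points. The entry value precedes the programme, so this average does not measure a programme effect.

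**The case against.** The strongest reply is that 0.183 SD is a single-value comparison, whereas the article gives 0.14 SD for longitudinal models with two measures per subject. Baseline adjustment is a standard analysis, and 467 vs 467 gives 0.139 SD at a correlation of 0.65 and 0.131 at 0.7. This stands: 0.14 SD is attainable between two territories. It does not show how the figure was obtained, because the article treats effective covariables as a further gain beyond the stated calculation, and no correlation is given.

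Likewise, 9 points is close to the worst case for a proportion. Baseline adjustment would help here too. As an illustration under assumptions, a continuous correlation of 0.7 corresponds to about 0.49 after a median split; then 9.1 × √(1 − 0.49²) ≈ 7.9 points at 50% and 8.0 × 0.872 ≈ 7.0 at 70%. So 7 points can be reached for some outcomes, but not across the range.

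A third reply is that an article may leave the correlation and reference proportion to a fuller document. That is fair, and their absence alone is not the point. The point is that the printed figures do not follow from the printed inputs for the contrast they name.

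A reader might also infer that the word conservative is wrong because patients share physicians and clinics. The text does not support that: "These calculations are conservatively based on the number of subjects measured twice" refers only to the number of measurements per subject. The article gives no cluster size or intraclass correlation from which to put a number on clustering.

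**Conclusion.** The point holds in a limited form. With equal territories and two-sided testing, the stated inputs give about 0.18 SD and up to about 9 points for a simple comparison of two territories. That is about 30% above the stated values (0.183/0.14 = 1.31; 9.1/7 = 1.30). Power at the stated values is about 57% in that analysis (for the binary figure, near 50% attainment). For a programme effect, the two stated figures together need a fairly high within-patient correlation and, if attainment is compared unadjusted, a proportion towards one end of the scale. Neither condition is stated.

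Two stronger readings are not supported. One is that 0.14 SD and 7% cannot be achieved; they can, under the conditions above. The other is that the authors computed one territory against the other five and mislabelled it. That contrast matches both figures, but so does an average of entry and follow-up values at a low correlation, and the article does not say which, if either, was used.

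The article itself concedes that six territories are few for comparative analysis, and nothing in it says how non-significant differences will be read. The risk of over-reading them is therefore an inference.

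**What to change.** Either of two changes to the power paragraph would do.

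1. Restate the figures, for example: *about 0.18 SD and up to about 9 percentage points between two territories (about 467 patients each), before any gain from baseline adjustment or repeated measures and before any allowance for clustering by physician or clinic.*
2. Keep 0.14 SD and 7%, and state beside them the contrast, the patients per territory, the within-patient correlation, the reference proportion and the sidedness that produce them.

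The text should not say that the present figures apply to one territory against five unless the investigators confirm that this was the calculation.

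The cost is wording and a less favourable sensitivity statement under the first option. No extra patients are needed and the design does not change.
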